### Procedure

**Table 1** demonstrates an overview of the process involved for coach and athlete participation for each condition. In summary, the intervention period starts in week 1 and ends in week 12. Coaches and athletes in each condition provide measures prior to week 1. Then, coaches in the intervention condition will receive the first workshop in week 1 and the second workshop in week 5. Coaches in the control condition receive their workshop in week 1. Coaches in the intervention condition are given weekly tasks each week up to week 12. The weekly tasks in the first 4 weeks focus on planning activities that aim to increase the use of need supportive communication and avoid or minimize the use of need thwarting behaviors when coaches are interacting with their athletes. The weekly tasks in weeks 5–12 focus on planning activities that aim to help coaches to initiate discussions about doping issues using a need supportive communication style. As explained earlier, coaches are assisted in these weekly activities via a number of resources available in their workbooks and via the private Facebook group. Coaches and athletes in both arms provide assessments after the intervention, that is, in week 13, as well as 2 months later. The coaches in the control condition will receive the motivational workshop (and all associated resources) after all assessments have been completed. However, due to resource constraints, they will not have the ongoing support from us should they wish to put in practice what they have learned.

**Table 1 T1:** The SPIRIT schedule of enrolment, interventions, and assessments.

[figure not shown]

To promote participant retention, athletes will be entered into a prize draw to win monetary retail vouchers if they complete all assessments. In order to promote retention of coaches in the trial, the research team will be in regular contact with them throughout the intervention period via phone and email. There will be no other data collected from athletes or coaches if they refuse to continue participation in the study. All coaches will receive a certificate from the research team and a monetary retail voucher if they complete all aspects of the project.

The workshops will be delivered by our research team members who have expertise in psychology and experience in delivering workshops about motivation or anti-doping to coaches and athletes. To standardize the delivery of the workshops across countries, presenters at the workshops will be trained using video recorded demonstration workshops and detailed slide notes. The workshops will take place in a prearranged central location with access to suitable teaching facilities (i.e., close seating arrangements, projector). These locations include university campuses, local sport and recreation departments, or at participating sporting clubs or organizations.

### Measures

#### Questionnaires

Two questionnaire packs (one for coaches and one for athletes) with the same questions will be administered at all three time-points (with the exception of questions about demographics which will be administered at baseline). Participants will be matched up across time points by a unique ID code given to them by the research team. The questionnaire packs include new questionnaires developed by us for the purposes of this project as well as questionnaires that are already available in the literature; we refer the reader to the original sources for information on the psychometric properties of established questionnaires.

##### Athlete questionnaire pack

(1)Willingness to take potentially prohibited substances (Whitaker et al., 2014). It consists of nine items, scored on a 1 (*not at all willing*) to 7 (*extremely willing*) scale. The stem is “Would you be willing to use a banned substance if you…”: An example item is: “Have been heavily underperforming?”(2)Moral disengagement in doping (Kavussanu et al., 2016). It consists of six items, scored on a 1 (*strongly disagree*) to 7 (*strongly agree*) scale. An example item is: “Doping is alright because it helps your team.”(3)Attitudes toward doping (Barkoukis et al., 2013). It consists of eight items, scored on a 1–7 scale with opposite adjectives. The stem is “How do you feel about doping?” An example item is: “Harmful” (scored as 1) and“Beneficial” (7).(4)Efficacy to resist doping-related temptations (Barkoukis et al., 2013). It consists of six items, scored on a 1 (*no confidence*) to 7 (*complete confidence*) scale. The stem is “How confident would you be that you could resist the temptation to use banned substances even if…?” An example item is: “Your teammates or other competitors were using these substances?”(5)Self-reported use of performance/recreational substances and drugs. This variable is assessed with a new measure developed by the research team. We list 13 groups of substances and products, some legal (e.g., creatine) and some illegal (e.g., anabolic steroids), and ask athletes whether they have used any of those in the last 12 months (in the first assessment) or since last completing the questionnaire (in the next two assessments).(6)Knowledge about anti-doping testing procedures. This variable is assessed with a new measure developed by the research team and based on current NADO knowledge assessment approaches. It is presented in the form of a quiz with six questions with three possible answers (*True, False, I Don’t Know*). An example is: “If a nutritional supplement is bought from the pharmacy (over-the-counter), it will not contain a banned substance.”(7)Behaviors to prevent unintentional/inadvertent doping. This variable is assessed with a new measure developed by the research team. We list six behaviors and we ask athletes to indicate with a *Yes* or *No* answer whether they have engaged in this behavior in the last 4 weeks. An example is: “Checked if my supplements, food and/or drinks contain banned substances.”(8)Perceived need supportive and need thwarting coach behaviors (Interpersonal Behaviors Questionnaire (IBQ) in Sport; Rocchi et al., 2017). It consists of 24 items, scored on a 1 (*strongly disagree*) to 7 (*strongly agree*) scale. The stem is “Over the last 4 weeks, my coach….” An example item for need support is: “Supported my decisions” and for need thwarting is: “Imposed their opinions on me.”(9)Satisfaction (Bartholomew et al., 2011a) and frustration of psychological needs (Bartholomew et al., 2011b). Fifteen items measured the satisfaction of the three psychological needs and 12 items measured the frustration of those needs. All items were scored on a 1 (*strongly disagree*) to 7 (*strongly agree*) scale. An example item for need satisfaction is: “I have a say regarding what skills I want to practice” and for need frustration is: “I feel forced to follow training decisions made for me.”

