### Hypotheses

•Compared to their baseline levels and to athletes in the control condition, athletes whose coaches complete the training will report: (1) less willingness to take potentially illegal substances (primary outcome), (2) higher perceptions of need supportive and lower perceptions of need thwarting coach motivational strategies (our manipulation check), (3) less favorable attitudes, (4) lower moral disengagement toward doping, (5) higher efficacy to resist doping-related temptations, (6) increased knowledge about anti-doping procedures, and (7) more behaviors to prevent unintentional/inadvertent doping. We also measure self-reported use of performance/recreational substances and drugs, but given that previous studies have found that only 10% of athletes admit to doping use (e.g., Barkoukis et al., 2013; Ntoumanis et al., 2017a), we do not expect to have statistical power to detect significant changes in such use.•The intervention effects on doping-related variables will be mediated via increased psychological need satisfaction/reduced need frustration in the athletes in the experimental condition.•Compared to their baseline levels and to coaches in the control condition, coaches who complete the intervention will (1) utilize more need supportive and less need thwarting communication strategies when discussing doping related issues with their athletes, (2) report higher efficacy to discuss doping with athletes and create an anti-doping atmosphere within the team, (3) rate need supportive communication styles as being more effective (need thwarting style as less effective) in dealing with a doping-related situations, (4) have better knowledge about anti-doping testing procedures, (5) encourage their athletes to use more inadvertent doping prevention behaviors, (6) report stronger anti-doping attitudes, and (7) report lower moral disengagement in doping.•There is insufficient prior evidence to put forward hypotheses regarding any cross-cultural differences in the effectiveness of the intervention.

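### Self-reported substance use is asked over about 12, 3 and 2 months, so the three answers cannot be read as change over time

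*Protocol article*

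**What the plan says.** Item 5 of the athlete questionnaire pack lists 13 groups of products, some legal and some not. The team will "ask athletes whether they have used any of those in the last 12 months (in the first assessment) or since last completing the questionnaire", the second form applying at the two later assessments.

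The Procedure section sets the timing: "Coaches and athletes in each condition provide measures prior to week 1", and both arms "provide assessments after the intervention, that is, in week 13, as well as 2 months later".

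The Questionnaires section describes packs "with the same questions will be administered at all three time-points" and excepts only the demographic questions.

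Under Hypotheses, the athlete outcomes numbered (1) to (7) are introduced by "Compared to their baseline levels and to athletes in the control condition". Substance use is not among them. It is mentioned afterwards as also measured, with the remark that "we do not expect to have statistical power to detect significant changes in such use", because "previous studies have found that only 10% of athletes admit to doping use".

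The Analyses section plans multilevel models for the questionnaire data that take account of their longitudinal structure. It does not mention recall length.

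**The concern.** A yes/no report of any use depends on how long a period it covers. With behaviour held constant, a shorter window can leave the proportion answering yes the same or lower it, but cannot raise it. The artefact therefore runs one way, towards apparent improvement. Items 7 and 8 of the same pack use a constant four-week window, so they do not have this problem.

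The wording of the later question also ties the window to attendance. An athlete who skips week 13 and returns at follow-up reports on the whole period since baseline, while an athlete who attended both reports on only the last two months.

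This is the only item in the article that records actual use rather than attitude or willingness. The results are to go to anti-doping bodies and the media. A time effect or within-arm fall in use should not be put before those readers if the recall window could account for it.

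**Working it through.** The article gives no expected change in use, so there is no figure of its own to reproduce. The check asks what the three questions would return if behaviour did not change at all.

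**Inputs from the article**
- Window at baseline: 12 months (item 5).
- Window at the second assessment: from before week 1 to week 13, about 13 weeks (item 5 with Procedure).
- Window at the third assessment: 2 months, about 9 weeks (same sources).
- Admitted doping in previous studies: 10% (Hypotheses).

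**Assumptions**
- The 10% is a 12-month rate. The article gives no recall period for it.
- A share *s* of 12-month users use continuously; the rest use sporadically at a constant rate. The article gives no value for *s*, so the full range is shown.

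**Formula.** With 12-month prevalence *p* and window *w* in years, the expected proportion reporting use is p·s + 1 − (1 − p(1 − s))^w.

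**Purely sporadic use (s = 0, p = 0.10)**
- Week 13: 1 − 0.9^(13/52) = 0.026. Apparent fall 1 − 0.026/0.10 = 74%.
- Follow-up, window taken as 2/12 year: 1 − 0.9^(2/12) = 0.0174. Apparent fall 83%.
- Follow-up, window taken as 9 weeks: 1 − 0.9^(9/52) = 0.0181. Apparent fall 82%.

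**Other mixes (p = 0.10, follow-up window 2/12 year)**

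| Share continuous | Week 13 | Fall | Follow-up | Fall |
|---|---|---|---|---|
| 0% | 2.6% | 74% | 1.7% | 83% |
| 25% | 4.4% | 56% | 3.8% | 62% |
| 50% | 6.3% | 37% | 5.9% | 41% |
| 75% | 8.1% | 19% | 7.9% | 21% |
| 100% | 10% | 0% | 10% | 0% |

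The relative falls depend little on the assumed prevalence. For purely sporadic use they are 75% and 83% at p = 5%, and 68% and 78% at p = 50%. With equal windows at all three assessments the artificial fall is zero in every row.

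**Could chance hide it?** Take 600 athletes per arm (half of 1200) and a design effect of 1 + 9 × 0.005 = 1.045, so an effective n of 600/1.045 = 574. In the purely sporadic case the standard error of the week-13 change is √[(0.10 × 0.90 + 0.026 × 0.974)/574] = 0.0142, and z = (0.10 − 0.026)/0.0142 ≈ 5.2. The same calculation at follow-up gives about 6.0. Both treat the time points as independent, so they are rough. They show that low power for a true effect is no safeguard against this artefact.

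**Skipping week 13.** Still with s = 0, an athlete who missed week 13 reports at follow-up on about 13 + 9 = 22 weeks: 1 − 0.9^(22/52) = 4.36%, against 1.81% for one who attended. As an illustration, suppose 30% of one arm and 20% of the other missed week 13 and all returned. Expected follow-up use differs by 0.10 × (4.36 − 1.81) ≈ 0.26 percentage points with no true effect. The article gives no information on whether missingness will differ by arm.

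**The case against.** The strongest reply is that the article plans nothing wrong with these answers. The comparison with baseline governs outcomes (1) to (7), and use is outside that list. The sentence on changes in use is a disclaimer about power, not a plan to test change. The modelling sentence under Analyses is general, and details for a measure without a hypothesis are commonly left to an analysis plan. The windows also have a good rationale: repeating a 12-month question at week 13 would mix about nine pre-intervention months into the answer. Both arms are asked the same question on the same schedule, so the randomised comparison is protected.

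Much of this stands. A reader might infer that a change-from-baseline test of use is planned; the article does not say so. A reader might also infer that the arm comparison is biased. Under no effect it is not, except for the small and hypothetical missingness effect above. The later windows are sensible for separating use after baseline from earlier use, and the questionnaire need not change.

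What remains is that the article itself fixes the unequal windows, describes the questions as the same throughout, assigns the questionnaire data to longitudinal modelling, and gives power as its only reservation about changes in use. Applied to item 5 as written, that framework yields a time effect biased towards a fall, and nothing stated corrects it. That is more than an omitted detail.

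**Conclusion.** The point holds as a limited one. The baseline and later answers to item 5 are not comparable, and any time effect or within-arm change computed from them is biased towards a fall unless all use is continuous.

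A reader might go further and expect a large spurious fall. The article does not support that. The range is 0% to about 74% at week 13 and 0% to 82–83% at follow-up, and the deciding quantity, the mix of continuous and sporadic use, is not given. The upper figures also borrow a 10% rate quoted for admitted doping, whereas item 5 includes legal products such as creatine that may be taken regularly. They are bounds under a constant-rate assumption, not forecasts.

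The primary outcome, the numbered hypotheses and the sample size are unaffected. This is a minor improvement, worth making because it is cheap.

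**What to change.** State that use is not analysed or reported as change from baseline or as a trend over the three assessments. Compare the arms in one of two ways, with the 12-month baseline answer as a covariate only:

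- on use at each post-baseline assessment, accounting for the length of the window; or
- on any use since baseline, combining the two later reports. For every athlete who answers at follow-up this covers about 22 weeks, whether or not week 13 was skipped.

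The window adjustment needs completion dates, which the article does not say are recorded. If they are not, whether week 13 was attended still separates the 9-week from the 22-week reports. The Questionnaires section should also note that item 5 changes its recall period.

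The cost is a few sentences, slightly more analysis work, and no within-arm estimate of change in use. The questionnaire stays as it is, so data already collected in Australia remain usable.

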
##### Coach questionnaire pack

(1)Moral disengagement (moral disengagement in doping scale, Kavussanu et al., 2016). See athlete questionnaire pack.(2)Attitudes toward doping (Barkoukis et al., 2013). See athlete questionnaire pack.(3)Efficacy to discuss with athletes about doping (Doping Confrontation Efficacy Scale, Sullivan et al., 2015). This variable is a 20-item scale, but we are using seven items only as the rest of the questions mix discussions about doping and communication style used in such discussions (e.g., “how confident are you in your ability to confront athletes about PEDs while avoiding personal criticism?”). Unlike Sullivan et al. who used a 1–7 scale, we used a 0% (*no confidence*) to 100% (*complete confidence*) scale, as such a scale is more common in the self-efficacy literature (Bandura, 1997). An example item from those we are using is: “How confident are you in your ability to discuss banned substances and methods with an athlete?”(4)Perceived effectiveness of need supportive and need thwarting communication styles in dealing with a situation in which a coach suspects an athlete in their team has used a banned substance. This variable is assessed with a new measure developed by the research team. We developed 10 items, five for a need supportive style and five for a need thwarting style; these items are scored on a 1 (*very ineffective*) to 7 (*very effective*) scale. An example item of the former style is: “Demonstrating affection and care,” and of the latter is: “Impose rules with no explanations.”(5)Efficacy to create anti-doping atmosphere within the team. This variable is assessed with a new measure developed by the research team. We wrote four items which are scored on a 0% (*no confidence*) to 100% (*complete confidence*) scale. An example is: “How confident are you to create a culture within your athletes in which doping is not valued?”(6)Knowledge about anti-doping testing procedures. See athlete questionnaire pack.(7)Encouragement of athletes to engage in behaviors to prevent unintentional/inadvertent doping. This variable is similar to the ‘behaviors to prevent unintentional/inadvertent doping’ questionnaire in the athlete pack, but it has been modified to ask coaches whether they have encouraged their athletes to engage in those behaviors.

##### Fidelity assessment

Coaches are also asked to participate in a semi-structured role play. During the role play, a trained research assistant plays the role of an athlete considering taking banned substances while the coach responds in ways which they would consider as a typical response from them. In this hypothetical scenario, a 23-year-old athlete has experienced a performance ‘plateau’ in that they haven’t seen their performance improve over the last 12 months. They are considering taking performance enhancing supplements to break this trend. The role play typically lasts about 20 min and takes place on two occasions, before the intervention and after the end of it, as indicated in **Table 1**. The role plays are audio recorded so that they can be coded later on in terms of the communication style used by the coach. We will use an observational scale (Quested et al., under review) with trained raters, blinded to the experimental condition, to rate the frequency and intensity of need supportive and need-thwarting communication used in these discussions. The aim of this assessment is to establish whether the intervention arm coaches’ communication during the second role play demonstrates fidelity to the intervention (i.e., “treatment enactment”; see Borrelli, 2011), and also to compare the ratings of the coaches in the two arms at each time point. A more rigorous test would have been to code actual communications between coaches and their athletes, however, this was not feasible due to resource constraints as well as the logistical and ethical challenges of filming such discussions. Our role playing is, hence, a proxy measure of fidelity to treatment enactment. We have followed many of Borrelli’s recommendations to enhance fidelity throughout the research process including study design (e.g., explicit use of a theoretical model, pilot testing, and feedback from participants), training (standardized training, accommodate learner differences, assess skill acquisition, and prevent skills drift), treatment delivery (interviews at the end of the project, use of a manual), and treatment receipt (e.g., present material in an engaging way, assess confidence to apply the skills delivered).

### Phase 3

In this last phase of the project, we will implement a thorough process evaluation of the intervention via coach and athlete interviews, coach questionnaires on ease and usefulness of the training material, as well as fidelity to the protocol assessments. We plan to interview either individually or in a group format between 5 and 10 coaches and athletes in each country from the experimental condition. The purpose of the interviews with the coaches will be to ascertain their views on the training they received and its different components (e.g., workshops, online material). We will establish which components the coaches liked or disliked (and why), and how often they engaged with those components in their coaching practice. We will also discuss successes and challenges the coaches experienced in integrating the training material in their coaching practice. Suggestions will also be sought from the coaches in terms of material modification and, more generally, in terms of program modification. This qualitative information will be combined with quantitative ratings that coaches (from both arms) will provide at the end of each workshop and at the end of the study. These ratings will provide evaluations of the perceived usefulness and clarity of the different components of the training and the coaches’ efficacy in utilizing those. The interviews with athletes will establish whether the athletes noticed any changes in their coaches’ communication (in terms of content and style) about (anti)doping from before to after the program.

Limitations of the project include the lack of strong fidelity data as to whether the coaches will implement the taught strategies with their athletes, the use of self-reported data for doping use, and also the fact that the anti-doping education will be delivered by researchers and not by practicing anti-doping educators. Also, other influences on athletes’ tendencies to engage in doping, besides the coach influence, such as societal pressures or organizational pressures at the sport club level are not assessed in this project. Another potential limitation of the project is that the two groups will receive unequal attention in terms of hours of face-to-face contact and online support (related to the implementation of need supportive communication). It would not have been desirable to offer similar amount of time to the control group because there is only so much fuctual information about anti-doping procedures and banned substances one can deliver in an engaging way in face-to-face workshops. Our current 1-h workshop for the control group reflected current anti-doping practice in the three countries. The other option would have been to cut down our motivation intervention to a 1-h workshop and provide nothing more. However, the meta-analysis by Su and Reeve (2011) shows that SDT interventions need to be fairly extensive to be effective. Having a third group (attention control) would have also not been financially feasible given the size of the project. On the other hand, intensive interventions do not necessarily produce more positive results. For example, such interventions can result in participant attrition due to lack of time for engagement from the participants.

